# The effect of gold kiwifruit consumed with an iron fortified breakfast cereal meal on iron status in women with low iron stores: A 16 week randomised controlled intervention study

**DOI:** 10.1186/1471-2458-10-36

**Published:** 2010-01-26

## Abstract

**Background:**

Dietary treatment is often recommended as the first line of treatment for women with mild iron deficiency. Although it is well established that ascorbic acid enhances iron absorption, it is less clear whether the consumption of ascorbic acid rich foods (such as kiwifruit) with meals fortified with iron improves iron status. The aim of this study is to investigate whether the consumption of ZESPRI^® ^GOLD kiwifruit (a fruit high in ascorbic acid and carotenoids) with an iron fortified breakfast cereal meal increases iron status in women with low iron stores.

**Methods/Design:**

Eighty nine healthy women aged 18-44 years with low iron stores (serum ferritin (SF) ≤ 25 μg/L, haemoglobin (Hb) ≥ 115 g/L) living in Auckland, New Zealand were randomised to receive an iron fortified breakfast cereal (16 mg iron per serve) and either two ZESPRI^® ^GOLD kiwifruit or a banana (low ascorbic acid and carotenoid content) to eat at breakfast time every day for 16 weeks. Iron status (SF, Hb, C-reactive protein (CRP) and soluble transferrin receptor (sTfR)), ascorbic acid and carotenoid status were measured at baseline and after 16 weeks. Anthropometric measures, dietary intake, physical activity and blood loss were measured before and after the 16 week intervention.

**Discussion:**

This randomised controlled intervention study will be the first study to investigate the effect of a dietary based intervention of an iron fortified breakfast cereal meal combined with an ascorbic acid and carotenoid rich fruit on improving iron status in women with low iron stores.

**Trial registration:**

ACTRN12608000360314

## Background

Iron deficiency is the most common nutritional deficiency worldwide and is common in premenopausal women [1]. In the 1997 New Zealand National Nutrition Survey low iron stores, iron deficiency and iron deficiency anaemia mainly affected women aged 15 to 44 years of age [2]. Iron deficiency is a concern due to its association with impaired work performance, cognitive function and immunity [3-5].

Mild iron deficiency can be effectively treated through dietary intervention [6]. This can include the addition of iron containing foods to the diet, such as foods fortified with iron [7], or improving the bioavailability of iron within meals [8]. Zimmerman et al [9] found that adding 12 mg of iron per day to snack foods increased iron status in Thai women with low iron stores. Snack foods fortified with ferrous sulphate improved iron status to a greater extent than snack foods containing electrolytic and hydrogen-reduced iron [9]. It is well established that ascorbic acid enhances iron absorption when added to meals [10,11]. Carotenoids including lutein and zeaxanthin have been shown to enhance iron absorption when added to a wheat based breakfast [12]. It is less clear whether the enhanced iron absorption by the addition of ascorbic acid or carotenoids to meals over time will improve iron status.

Studies investigating the effect of consuming ascorbic acid with meals have shown little or no effect on iron status [13-16]. Cook [13] found that consuming 1000 mg ascorbic acid with meals twice per day over 16 weeks did not improve iron status in seventeen healthy males and females who had a range of iron stores. Four subjects whose initial serum ferritin was <10 μg/L did however, improve their iron status. Subjects with normal iron stores are known to absorb iron less efficiently than women with depleted iron stores [17]. A study in eleven iron depleted women found that providing 500 mg ascorbic acid with three meals per day for five and a half weeks improved haemoglobin levels but not serum ferritin levels [15]. Using a cross over study design, Hunt et al [14] found that 500 mg ascorbic acid provided with meals three times per day for five weeks improved serum ferritin slightly but not significantly in twenty five iron depleted women consuming typical Western diets or diets of poor iron bioavailability. No changes in serum ferritin levels were seen in fourteen vegetarian subjects who consumed tofu alone or tofu and orange juice for 30 days in a cross over study [16]. Limitations of these studies include small sample sizes, three of the studies being of less than six weeks duration, and in some cases, the use of subjects with normal iron stores or whose iron levels was not reported. A well designed study by Garcia et al [18] found the addition of 25 mg of ascorbic acid as lime juice to two meals per day for eight months did not improve iron status in eighteen iron deficient Mexican women compared to a control group consuming a lime flavoured beverage with no ascorbic acid [18]. However, many of the reported studies have not stated the iron content of the meals to which ascorbic acid was added [13] or have only reported total daily iron intake [14,15,18]. In the one study that did report the iron content of the meals to which ascorbic acid was added, only 2.24 mg of iron was consumed at each meal [16]. Ascorbic acid promotes iron absorption by chelating iron in the intestinal lumen and promoting acidic conditions so that dietary iron is solubilised, preventing iron from binding to inhibitory ligands [19]. Ascorbic acid may therefore be more likely to improve iron status if consumed with meals containing substantial amounts of fortificant iron [20].

It is hypothesized that iron absorption from a breakfast cereal fortified with iron will be enhanced if consumed with kiwi fruit as kiwi fruit is a rich source of ascorbic acid (108.9 mg/100 g), lutein and zeaxanthin (307.9 μg/100 g) [21] and will consequently result in improved iron status. This study therefore aims to investigate whether consuming kiwifruit with a breakfast cereal fortified with 16 mg iron (1.92 mg natural iron, 14.08 mg iron in the form of ferrous sulphate) improves iron status in healthy women with low iron stores compared to a fruit low in ascorbic acid, lutein and zeaxanthin (banana).

## Methods/Design

The study design is illustrated in Figure 1. The first phase of the study involved screening of 626 women to identify women with low iron stores. Phase two involved a randomised controlled intervention where women consumed iron fortified breakfast cereal and fruit every day at breakfast time for 16 weeks.

**Figure 1 F1:**
[figure not shown]
**Study design**. The effect of gold kiwifruit consumed with an iron fortified breakfast cereal meal on iron status in women with low iron stores: A 16 week randomised controlled intervention study

### Subjects

It was calculated that a minimum of 42 subjects with low iron stores would be required in each group to demonstrate a significant difference in serum ferritin of 2.5 μg/L at 80% power and 5% significance (two sided test). Power calculations were based on a standard deviation for serum ferritin of 4.1 μg/L (determined from a group of iron deficient women measured in our laboratory) (unpublished observation) and 2.5 μg/L was considered a possible clinically important difference. More subjects (n = 89) were recruited to allow for drop-outs from the study.

### Inclusion/exclusion criteria

Women aged 18-44 years with low iron stores (serum ferritin ≤ 25 μg/L and haemoglobin ≥ 115 g/L) were included in this study. A serum ferritin of ≤ 25 μg/L has been reported to be a clinically relevant cut off to demonstrate increased iron absorption with dietary factors [22]. Subjects were excluded from the study if they were pregnant, breastfeeding or if they had any known health problems likely to influence iron status including inflammatory bowel disease, coeliac disease, a history of gastric ulcers, disorders of red blood cells, menorrhagia, haemorrhoids, haematuria or malaria. Women who reported any allergies or intolerances to kiwifruit, bananas, milk or any of the components in the breakfast cereal were also excluded from the study. The women had to be willing to consume breakfast cereal, milk and kiwifruit or a banana for breakfast every day for a sixteen week period. Subjects had to be prepared not to donate blood nor to consume iron, ascorbic acid or calcium supplements (or supplements containing these nutrients) for the duration of the study, or to have regularly consumed iron supplements within the three months prior to participating in the study.

### Setting and recruitment

The study took place in Auckland, New Zealand. Subjects were recruited from the Auckland area using a variety of recruitment techniques. Women with low iron stores who had participated in a previous study [23] investigating the iron status of female university students conducted in our laboratory were invited to take part (n = 51). A web site was set up where women could find information about and register their interest in the study. Women were also recruited using newspaper advertisements that were placed in two local papers distributed free of charge to residents living on the North Shore of Auckland, New Zealand. An article written about the study was published in newspapers throughout Auckland region. A New Zealand magazine about healthy eating advertised the study via their monthly email newsletter. Forty six local primary schools were contacted and several advertised the study in their school newspaper. The study was also advertised using Facebook (a social networking site) and through emails sent to colleagues. The study was verbally promoted at local events attended predominantly by women (for example, a gym, a preschooler's library session, a cooking class and at a netball match). Posters and flyers were printed to advertise the study. A large number of flyers were delivered to houses on the North Shore, Auckland and researchers provided local businesses with flyers. Various businesses advertised the study on their websites.

### Screening

Women who expressed an interest in taking part in the study were provided with an information sheet and asked to complete a consent form and screening questionnaire and return these by post. The screening questionnaire asked questions to ensure subjects met the inclusion criteria for the study. A blood sample was taken at Diagnostic MedLab Ltd, Auckland or Massey University, Auckland by qualified phlebotomists. The blood sample was used to determine serum ferritin (SF), haemoglobin (Hb) from a complete blood count (CBC) and C-reactive protein (CRP). CRP was measured as raised CRP is associated with infection and may falsely elevate serum ferritin [24]. Women who had a serum ferritin ≤ 25 μg/L and haemoglobin ≥ 115 g/L were invited to continue with phase two of the study. Women with raised CRP (>5 mg/L) were invited to have a second blood test three weeks after the first blood test. All blood results were reviewed by a medical practitioner. Women with abnormal blood results including iron deficiency anaemia (SF<20 μg/L, Hb<115 g/L) were sent a copy of their results and advised to consult their general practitioner. Women with normal iron stores were sent a letter advising them of their results.

### The intervention - an overview

Refer to Figure 1. Women who met the criteria for the study were randomised into two groups. Both groups consumed a specially developed iron fortified breakfast cereal and milk at breakfast time for a 16 week period. One group consumed two ZESPRI^® ^GOLD kiwifruit with their breakfast. The other group (the control group) consumed a banana with their breakfast. Subjects were asked to consume this breakfast daily. Subjects came into the Human Nutrition Unit at Massey University before and after the 16 week period for baseline and final measures. At both visits the subjects gave a fasted blood sample, had anthropometric measures done, completed a face to face interview, and a physical activity questionnaire (see Table 1). Online questionnaires were completed at both visits. These included questionnaires about dietary intake and blood loss. Guidelines for completing the study were given at the first visit. Each visit took no longer than 2 hours.

**Table 1 T1:** Outcome measures and testing methods used

Anthropometric and clinical assessments	
Height, weight, waist and hip circumference (baseline and end)	ISAK anthropometry protocol, electronic scales, stadiometer, Lufkin tape

**Questionnaires**	

Face to face interview (baseline)	Demographics, medical history, supplement use

Physical activity (baseline and end)	New Zealand Physical Activity Questionnaire Short Form (NZPAQ-SF) [26]

Dietary intake (baseline and end)	FFQ (iron containing foods, foods known to affect iron absorption)

Blood loss (baseline and end)	Adapted blood loss questionnaire [28]

Evaluation (end)	9 point hedonic scales to determine overall acceptability, appearance, flavour and texture [30]; 5 point just right scale regarding amounts of food [30]; food action rating scale (FACT) [31]; compliance diary

### Randomisation of subjects

Eighty nine women were recruited to take part in the intervention phase of the study. Subjects were matched in pairs according to their serum ferritin level and age. Each subject was randomly allocated to either the kiwifruit group or banana group by a coin toss. Forty four women were allocated to the kiwifruit group and forty five women to the banana group.

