### Data handling and statistical analysis

Statistical analysis will be performed using SPSS for Windows Version 16 (SPSS Inc., Chicago, IL, USA) [32]. Name and contact details of all subjects are stored in a database, in individual files and in Microsoft Excel. Data will be entered in to a single Microsoft Excel spreadsheet with subjects identified only by their unique study number. All entered data will be checked by another member of the research team to ensure it has been entered accurately prior to statistical analysis.

Descriptive statistics will be used to describe the baseline population using mean (standard deviation), median (25, 75 percentile) or frequencies summary statistics. Normality of distribution will be evaluated using the Kolmogorov-Smirnov test.

Non-normally distributed variables will be transformed into approximately normal distributions by logarithmic transformations and again tested for normality.

The main analysis will be the effect of the intervention on serum ferritin concentrations. Analysis of covariance will be used to compare the kiwifruit and the banana groups at the end of the study while controlling for baseline serum ferritin concentrations. Comparisons will also be made within the kiwifruit and banana groups between baseline and endpoint measures using the dependent t-test. The effect of the intervention on haemoglobin, soluble transferrin receptor, soluble transferrin receptor: serum ferritin ratio, ascorbic acid and carotenoids between and within groups will also be investigated using the statistical methods described above. The data will be investigated for possible confounding factors and effect modifiers e.g. age, body mass index, blood loss and dietary intakes. If confounding factors exist, analysis of covariance will be used to analyse the effect of the kiwifruit compared to the banana on iron status while controlling for the effects of these confounding factors. Serum ferritin, soluble transferrin receptor, soluble transferrin receptor: serum ferritin ratio and ascorbic acid will be tested using one-sided tests. Two sided tests will be used for all other variables. Effect size (to check for type 1 errors) will be calculated and where a statistically non-significant effect is seen, post hoc power calculations will be conducted to find out if the sample size was sufficiently large enough to detect an effect (to check for type 2 errors). Significance will be set at p < .05.

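### Age was a matching factor, but the main ANCOVA lets it in only through a confounder check; fixing it in advance is a small, nearly free gain

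*Protocol article*

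**What the plan says.** The protocol article, under 'Randomisation of subjects', describes matching before allocation: "Subjects were matched in pairs according to their serum ferritin level and age". It continues: "Each subject was randomly allocated to either the kiwifruit group or banana group by a coin toss". The result was uneven by one: "Forty four women were allocated to the kiwifruit group and forty five women to the banana group". The article does not say whether one toss settled both members of a pair, nor how the woman without a partner was allocated.

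Under 'Data handling and statistical analysis', the main ANCOVA is to "compare the kiwifruit and the banana groups at the end of the study while controlling for baseline serum ferritin concentrations". No pair term is named. Age appears only in a list of candidates: "The data will be investigated for possible confounding factors and effect modifiers e.g. age, body mass index, blood loss and dietary intakes". Further adjustment is conditional: "If confounding factors exist, analysis of covariance will be used to analyse the effect of the kiwifruit compared to the banana on iron status".

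The 'Subjects' section sizes the trial without reference to pairs: "a minimum of 42 subjects with low iron stores would be required in each group". The target there is a ferritin difference of 2.5 μg/L, with an SD of 4.1 μg/L, 80% power and a two-sided 5% test.

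**The concern.** When allocation is restricted within matched pairs, the arms are alike on the matching factors by construction, and the estimated difference varies less from trial to trial than it would with unrestricted tosses. A model that omits a matching factor leaves that factor's variation in the residual, so it can report a standard error larger than the true one.

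Ferritin is in the main model and age is not. If the confounder check looks for imbalance between arms, successful matching makes age look harmless, and age is dropped however well it predicts final ferritin. At stake are intervals slightly too wide and some lost power.

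A second, less certain point concerns ferritin itself. It was measured at screening, while the baseline blood was drawn at the first study visit, when the women also appear to have received their first fruit. The value used for pairing may therefore have been the screening value, which is not in the model either.

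**Working it through.** **The plan's own figure.** The unpaired formula gives n per group = 2(1.960 + 0.842)² × 4.1² / 2.5² = 42.2, with 79.8% power at 42. The stated 42 is thus reproduced (43 if rounded up). It uses the unadjusted SD and takes no credit for baseline adjustment or matching.

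**Does the split reveal the procedure?** 89 women make 44 pairs plus one, so one toss per pair gives 44/45 when all are paired but one. Under 89 independent tosses, the probability of a 44/45 split in either direction is 2 × C(89,44) / 2⁸⁹ = 0.168. The split therefore does not settle the matter.

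**Size in general.** If residuals of pair members correlate at ρ after the model's covariates, an analysis that ignores pairing overstates the SE by the factor 1/√(1 − ρ): 1.026 at ρ = 0.05, 1.054 at 0.10 and 1.118 at 0.20. The share of the sample forgone is ρ itself, so 5% to 20% over that range. The article gives no value of ρ, and zero is possible.

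**One toss per pair, matched on baseline ferritin and age.** Simulation of 44 pairs, SD 4.1, 6,000 trials per setting. Assumed: normal data, baseline–final ferritin correlation 0.6, pairs formed within narrow ferritin bands by closeness in age. Planned ANCOVA:

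| Age–final ferritin correlation (assumed) | Model SE / true SE | Two-sided type I error | 95% CI coverage |
|---|---|---|---|
| 0 | 0.984 | 5.2% | 94.8% |
| 0.1 | 1.017 | 4.9% | 95.1% |
| 0.2 | 1.012 | 4.8% | 95.2% |
| 0.3 | 1.074 | 3.6% | 96.5% |
| 0.4 | 1.101 | 3.1% | 96.9% |

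The ratios carry simulation noise of about 0.01. A ratio of 1.101 corresponds to ρ = 1 − 1/1.101² = 0.175. With age added as a covariate, the ratio is 0.98 to 1.01 and type I error 4.7% to 5.5%.

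**Power for 2.5 μg/L under the same assumptions (4,000 trials).** With age correlation 0, power is 93.9% both as planned and with age added. At 0.2 it is 94.3% and 95.3%; at 0.3 it is 95.9% and 97.3%, a gain of 1.4 points.

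**One toss per pair, matched on a separate screening ferritin and age.** Assumed: screening, baseline and final ferritin equally correlated at 0.5 to 0.8; 4,000 trials per setting. The planned ANCOVA overstates the SE by about 3–4% with no age effect, 6–8% at age correlation 0.2 and 10–14% at 0.3, with type I error 2.4% to 4.7%. With screening ferritin and age added, the ratio is 0.98 to 1.01. A rerun gave the same pattern to within one or two points.

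**Independent toss per woman.** At age correlation 0.3 the planned ANCOVA has an SE ratio of 0.995 and type I error of 5.1%: no mismatch. The model SE still falls from 0.706 to 0.658 when age is added, so the covariate earns its place on precision alone if age predicts ferritin that well.

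**The case against.** The strongest reply is that the allocation sentence speaks of each subject being tossed. Read literally, matching never restricted allocation and the planned ANCOVA is valid. This stands: the documents do not establish that the reported standard errors mismatch the design, though a reader might infer it from the word 'matched'.

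It can also be said that the stronger matching factor, ferritin, is already in the model, and that age is listed first among the variables to examine. Both are true. The article does not say that confounders will be picked by imbalance alone, so the omission of age is likely after successful matching but not certain. Nor does it say which ferritin value was used for pairing. The timing of the visits suggests screening but does not prove it.

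A reader might go further and conclude that the benefit of matching is thrown away in a trial with almost no reserve. That is not supported. The estimate itself keeps the benefit of the balance; only the reported interval may be too wide. The sizing formula also ignores the power gained from baseline adjustment, which under the assumptions above lifts power well over 90%.

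What remains is that age was used to build the design, and its place in the main model is left to a data-dependent step.

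**Conclusion.** The point holds as a minor one. A design variable, age, is not fixed in the main model. If one toss decided each pair, the planned standard error is correct or somewhat too large: about 0–10% for age correlations of 0 to 0.4, and possibly up to about 14% if pairing used a separate screening ferritin. If tosses were independent, there is no mismatch and only a possible small gain in precision is missed.

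In no case examined does the omission produce an excess of false positives. A reader who expects ignored pairing to make significance too easy has the direction reversed.

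The gap between design and model is plain from the text. Its size is not: every percentage rests on assumed correlations, normal data and an assumed closeness of matching, and closer matching on age would raise the figures. Low severity.

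**What to change.** 1. Name age together with baseline ferritin as covariates in the main ANCOVA, included whatever the confounder check shows.
2. State which ferritin value was used for pairing. If it was the screening value, add it as a covariate too.
3. State whether one toss decided each pair and how the woman without a partner was allocated. If the toss was by pair, add a sensitivity model with pair as a random effect.

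Covariate adjustment is preferable to a paired test as the main analysis: it is valid under either allocation procedure and keeps both the unpaired woman and the partners of women who drop out. The data are already collected, since age and screening ferritin were needed to select and match the women. The cost is a sentence or two of wording and one or two degrees of freedom. The analysis is described in the future tense, so the change can be fixed before the outcome data are examined.
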